### Implementation outcomes

The implementation outcomes are acceptability, fidelity, adoption, integration, and sustainability (Supplemental Table 1). To assess implementation outcomes, a prospective process evaluation (PE) will be embedded in the trial that uses a mixed-methods approach derived from audit data, implementation checklists, surveys, and semi-structured interviews (Supplemental Table 2). The PE will be guided by the Medical Research Council framework for evaluating complex interventions at an early phase to identify barriers and facilitators to improve implementation of the care bundle.^
12
^
Figure 3 illustrates a logic model describing the implementation process.

**Figure 3. fig3-17474930251342888:**
[figure not shown]
Logic model illustrating the implementation process and its relationship to clinical and implementation outcomes. ^a^Supplemental Table 2 for more details on key implementation strategies. ^b^Supplemental Table 1 for more details on implementation outcomes.

## Data safety monitoring board

An independent data safety monitoring board (DSMB) will review the safety and outcomes of the study, the quality of the trial conduct, monitor protocol adherence, and provide feedback to the Steering Committee on the conduct of the study as appropriate. The DSMB will meet 6-monthly to monitor the study progress and safety. A formal interim analysis will be performed by an independent statistician, blind to the randomized allocation, after 50 sites have reached data maturity. These data will then be reported to the DSMB for review of participant safety and outcomes as well as the quality of trial conduct. The DSMB will monitor unblinded safety outcomes and provide reports to the Steering Committee and recommendations in relation to continuation or stopping the study. A detailed DSMB charter will be made available that specifies the safety monitoring procedure and stopping rules.

## Statistical considerations and methods

### Sample size calculation

This study is designed with 90% power (α = 0.05) to detect an effect size of 0.20 improvement in the mean score of the UW-mRS, which corresponds to a mean difference of 0.07 (standard deviation = 0.356) between the care bundle group and the standard care group. The sample size is based on the INTERACT3 trial, in which the mean difference in UW-mRS scores between usual care (0.58) and care bundle (0.62) groups was 0.04.^
11
^ Considering the inclusion of components of anticoagulant reversal as well as referral pathways to intensive care and neurosurgery, we assume the effect of the care bundle in I-CATCHER will be greater than in INTERACT3.

Recruitment of a minimum of 110 sites is anticipated. To demonstrate a treatment effect with 90% power and a two-sided type I error rate of 5%, each site will need to recruit an average of 15 participants per phase for a total sample size of 3300 patients (110 sites × 2 phases × 15 participants). Assuming 5% of participants will have a missing 180-day outcome data, a total of 3500 participants are required which corresponds to a mean of 16 participants recruited per period per hospital. These calculations assume a within-period intra-cluster correlation (ICC) of 0.05 and a two-period decay with a cluster autocorrelation of 0.8 which are consistent with data from the INTERACT3 and Head Position in Acute Stroke Trial. Calculations were performed using the Shiny CRT Calculator.^
13
^

### Statistical analysis

All analyses will be undertaken at the patient level on an intention-to-treat basis using a linear mixed model with a random site effect to account for within-cluster correlations. The model will include fixed effects for the batch as well as stratification variables (i.e. country and level of site) and will adjust for data collected during the baseline period as suggested by Hooper et al.^
14
^ The effect of the intervention will be estimated as the adjusted mean difference and 95% confidence interval. Secondary outcomes will be analyzed using a similar approach but with logistic regression for binary outcomes and assuming a proportional odds model for the ordinal analysis of mRS. A detailed analysis plan including mock tables will be finalized before unblinding and made publicly available.

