## Introduction

Spontaneous intracerebral hemorrhage (ICH) accounts for up to 15% of acute strokes in high-income countries (HICs), but over half of all new stroke-related deaths and disability worldwide.^
1
^ Although a decreasing incidence of ICH has been observed in some countries, the burden of ICH is set to increase in Europe and other countries over the coming decades due to the aging of populations and lifestyle changes.^
2
^

The lack of proven treatments for ICH has created a sense of pessimism in many physicians, variable uptake of guideline-recommended treatments, and unnecessary use of early withdrawal of care in these patients.^
3
^ The devastating effects of ICH and the scarcity of randomized evidence to support single interventions have produced a nihilistic approach and over-estimates of adverse outcomes.^
4
^ Several prognostic variables in ICH include hematoma volume,^
3
^ level of consciousness,^
5
^ intraventricular hemorrhage,^
6
^ degree of hematoma expansion,^
7
^ and use of antithrombotic drugs.^
8
^ Management strategies that aim to limit hematoma growth include early intensive blood pressure (BP) lowering, reversal of anticoagulation, management of hyperglycemia, and targeted neurosurgery that includes the use of minimally invasive surgery (MIS),^
9
^ decompressive hemicraniectomy,^
10
^ and other approaches.

While efforts continue to define the role of individual interventions, evidence has emerged of the benefits of bundles of care in ICH.^3,11^ In particular, the third INTEnsive care bundle with blood pressure Reduction in Acute Cerebral hemorrhage Trial (INTERACT3) showed that the implementation of a systems of care approach that comprised a care bundle protocol for intensive BP lowering and other management algorithms for physiological control within several hours of ICH resulted in improved functional outcome.^
11
^ However, as most of the 121 hospitals which participated in INTERACT3 were located in low- and middle-income countries (LMICs), and the care bundle was dominated by intensive BP lowering, there may be uncertainty over the effectiveness, specific components, and fidelity of implementation of a care bundle in HIC.

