### Randomization and blinding

An independent statistician will assign hospitals in a 1:1 ratio to the care bundle or usual care. Within each batch, participating sites will be stratified according to country and level of site (comprehensive tertiary with neurosurgeon services vs. secondary hospital without neurosurgeon services). Sites will be notified of their randomized group within 2 weeks of an agreed date before commencing the intervention. Treatment allocation is open label.

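### The stated primary model names no patient-level prognostic covariate; adding a few presentation severity measures would be a cheap gain in precision and robustness, not the repair of an error

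*Protocol article*

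**What the plan says.** The Statistical analysis section gives the primary model as a patient-level linear mixed model with a random site effect. On fixed effects it says: "The model will include fixed effects for the batch as well as stratification variables (i.e. country and level of site"). It also adjusts for data from the baseline period. Under Study design, that period is the usual-care phase before sites start their randomized arm. The sample size counts its patients separately ("110 sites × 2 phases × 15 participants"), so this adjustment carries site-level information, not the presenting characteristics of the patients being compared. Secondary outcomes follow a similar approach, with logistic and proportional-odds models. A detailed analysis plan is promised before unblinding; it is not among the documents at hand.

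Three other statements bear on the choice:

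- The Introduction says "Several prognostic variables in ICH include hematoma volume" and goes on to level of consciousness, intraventricular hemorrhage, hematoma expansion and antithrombotic use.
- The Discussion says that the trial covers all degrees of severity.
- Randomization and blinding states: "Treatment allocation is open label". Under Consent procedures, individual consent covers data registration and follow-up. In the randomized phase it is therefore sought when the site already knows its arm.

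**The concern.** Two things are given up when a model for a population this varied carries no severity term.

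**Precision.** With about 15 patients per site per phase, patient-level variation makes up a little over half of the variance of a site mean. Presentation severity would explain some of that. The gain has practical value because the design difference of 0.07 is well above the 0.04 seen in the trial on which the design is based.

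**Robustness.** Baseline-period data remove stable differences between sites. They cannot remove a change in who is enrolled, or who consents, that differs between arms once allocation is known. Patient-level covariates can do so, to the extent that the change is measured.

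**Working it through.** **Inputs (Sample size calculation; Randomization and blinding).** K = 110 sites, 1:1; m = 15 per site per phase; ICC ρ = 0.05; cluster autocorrelation 0.8; two-sided α = 0.05. For the effect, the article gives a standardised 0.20, "which corresponds to a mean difference of 0.07 (standard deviation = 0.356"). For the prior trial, "the mean difference in UW-mRS scores between usual care (0.58) and care bundle (0.62) groups was 0.04".

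**Step 1: reproduce the plan's power.** Treat the analysis as a comparison of randomized-phase site means adjusted for baseline-phase site means.

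- SD² = 0.356² = 0.12674
- Between-site part: 0.05 × 0.12674 = 0.00634
- Within-site part of a mean: 0.95 × 0.12674 / 15 = 0.00803
- Variance of a site-phase mean: v = 0.00634 + 0.00803 = 0.01436, of which 0.00803 / 0.01436 = 56% is patient-level
- Covariance between phases: 0.8 × 0.00634 = 0.00507; r = 0.00507 / 0.01436 = 0.353; r² = 0.125
- Variance of the effect: (4/110) × 0.01436 × (1 − 0.125) = 0.000457; SE = 0.0214
- Power for 0.07: Φ(0.07/0.02138 − 1.96) = Φ(1.31) = 90.6%. A t reference with 108 df gives about 90%.

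The stated 90% is confirmed with no severity covariate in the calculation.

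**Step 2: add severity.** Let presentation covariates explain a share R² of the within-site variance only. The within-site part becomes 0.00803 × (1 − R²), and the rest of step 1 is repeated. The article gives no R², so a range is shown.

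| R² (assumed) | Variance ratio | SE | Power, 0.07 | Power, 0.04 | Difference detectable with 90% power |
|---|---|---|---|---|---|
| 0 | 1.00 | 0.0214 | 90.6% | 46% | 0.069 |
| 0.1 | 0.93 | 0.0206 | 92.5% | 49% | 0.067 |
| 0.2 | 0.85 | 0.0198 | 94.3% | 53% | 0.064 |
| 0.3 | 0.78 | 0.0189 | 96.0% | 56% | 0.061 |
| 0.4 | 0.70 | 0.0179 | 97.4% | 61% | 0.058 |

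Example for R² = 0.2: the within-site part is 0.00642, v = 0.01276, r = 0.00507 / 0.01276 = 0.397 and r² = 0.158. The variance is (4/110) × 0.01276 × 0.842 = 0.000391, so SE = 0.0198.

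If the covariates explained the same share of between-site variance too, the gain would be larger: at R² = 0.4, SE 0.0166 and power 98.8% for 0.07.

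**Step 3: case mix, as an illustration only.** Suppose mean severity differs between arms by 0.1 SD in the randomized phase but not in the baseline phase. The bias is about 0.1 × √R² × 0.356, with R² here taken as a share of total variance. For R² = 0.2 it is 0.1 × 0.447 × 0.356 = 0.016, or 23% of 0.07. For R² = 0.4 it is 0.1 × 0.632 × 0.356 = 0.023, or 32%. With SE 0.0214, the two-sided type I error would be about 12% and 18% in place of 5%. Both the shift and R² are assumed; nothing in the article shows that such a shift will occur.

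**The case against.** The strongest reply is that nothing stated is wrong. The terms in the model match the design, the power calculation claims no benefit from severity, and covariate lists commonly belong in the analysis plan. That stands as a reason not to call this an error. It does not remove the point, because the article does set out the terms of its primary model, and a better set is available at little cost.

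Four stronger readings are tempting and not supported:

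- **That the model excludes patient covariates.** The text says what the model will include. It does not say that nothing else may enter, and the analysis plan may add terms.
- **That the covariates are already recorded everywhere.** The bundle's triggers in Table 2 use anticoagulant status, volume, intraventricular extension and consciousness, so capture is likely. But the article does not list the case report form fields. It leaves investigations in usual care to the clinical team, and a referral threshold for volume does not prove that a numeric volume is stored.
- **That enrolment will be selective, or that adjustment would cure it.** Selection is a risk, not a finding. The article describes consecutive capture and broad eligibility, and patient consent concerns data and follow-up. Follow-up assessors are blinded, which protects outcome assessment. Regression corrects only measured differences.
- **That severity explains most of the variance.** Patient-level variation is 56% of the variance of a site mean, but under the range assumed here adjustment lowers the variance of the effect by 7% to 30%.

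Nor does adjustment settle whether 0.07 is a realistic target: power for 0.04 stays at or below 61% across the range in the table.

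**Conclusion.** The point holds as an improvement worth making. The primary analysis as stated is valid and delivers its planned power; a reader should not infer that the trial is underpowered or the model biased by construction. What is forgone is precision (a standard error of 0.0206 to 0.0179 in place of 0.0214) and some protection against measured case-mix differences after open allocation. The size of the gain rests on an assumed R² of 0.1 to 0.4, on the plan's own ICC and autocorrelation, and on the covariates being available in both arms and both phases.

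**What to change.** Pre-specify in the primary linear mixed model a short set of covariates measured at presentation, before bundle treatment. Examples are age, level of consciousness or stroke severity, hematoma volume on the diagnostic scan, intraventricular extension, location and prior anticoagulant use. Leave out hematoma expansion, although the Introduction lists it as prognostic: it occurs after presentation, and the bundle may affect it. First confirm that each item is captured in both arms and in both phases, and drop any that is not.

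Impute missing covariate values by a simple method. Keep the stated model as a sensitivity analysis, and tabulate case mix by arm and phase.

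If the same covariates enter the logistic and proportional-odds models, the odds ratio being estimated changes, not only its precision. State that it is conditional on the covariates, or report a standardised marginal effect.

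The cost is a change to the model wording, some extra analysis work and a rule for missing covariates. If a chosen item proves not to be collected in usual care, there would also be a data-collection cost, or a shorter list. The choice is most credible if fixed before unblinding.

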## Consent procedures

The consent process follows two processes:

Hospital cluster consent: Sites will consent to participate in endorsing the Care Bundle as standard practice for managing patients with ICH.Patient/responsible informed consent: Consent is obtained for the registration of patient data in the eCRF and participation in follow-up. A next of kin will be consulted for patients unable to provide consent. The consent process may vary by country, depending on the decisions made by their Institutional Research Ethics Committee.

## Discussion

I-CATCHER aims to evaluate the effectiveness of a multi-component care bundle for spontaneous ICH compared to standard care across the full spectrum of ICH severity. To better reflect the broad range of characteristics of patients affected by ICH, I-CATCHER features broad inclusion criteria, narrow exclusion criteria, and an efficient consent process. These factors facilitate the rapid inclusion of the vast majority of ICH patients into the study, enhancing both the generalizability of the study and the rate of recruitment. The trial design will capture consecutive patients with ICH and allow continued intervention as more hospitals join. Unlike a conventional stepped-wedge cluster randomized controlled trial (RCT), the intervention effect in this design reduces the risk of confounding by background temporal trends, as only baseline and parallel comparison data are used to assess the effectiveness of the care bundle.

Alongside its randomized design, I-CATCHER has a clear focus on implementation science through the determination of clinical efficacy of the care bundle but also by enabling its sustainable integration into routine practice across all participating hospitals. Previous studies, including a clinical trial involving a similar care bundle intervention in LMIC, have demonstrated significant patient benefit. However, patient demographics varied considerably from those in HIC. I-CATCHER extends this investigation to HIC with established ICH protocols, aiming to determine whether a time- and target-based intervention, combined with direct referral to neurosurgery and intensive care, can further improve patient outcomes in these settings.

## Summary and conclusion

As the first international RCT comparing an ICH care bundle intervention with standard care in HIC, I-CATCHER seeks to provide critical insights into whether this approach can improve 6-month outcomes for ICH patients. If successful, I-CATCHER could lead to changes in future ICH guidelines and potentially lead to widespread adoption of the ICH care bundle intervention, offering significant benefits to a patient population that currently experience high rates of mortality and morbidity.

